#### Treatment fidelity

As shown in Table 1, two to six components will be delivered to participants, and the selected components in each experimental condition will be integrated seamlessly. The intervention will be administered through telephone/video-conferencing software (i.e. Zoom) by well-trained research assistants. Research assistants will be provided with 10 h of intensive training, which will include reading materials, structured role play and practice opportunities for each component. Under experimental condition 1, in which participants will receive six components, the intervention will consist of 16 weekly sessions of approximately 45 min each as well as three booster support group sessions that will take place at 1, 2 and 4 months after the completion of the intervention. The intervention will be completed in 6 weeks under experimental conditions 8, 12, 14, 15 and 16, in which participants will receive only two components.

To ensure treatment fidelity, interventionists will submit an audiotape of their first implementation of a component session for review and receive feedback from the research team. We will monitor and maintain intervention implementation through weekly supervision meetings and monthly conference calls, which will involve all interventionists. Interventionists will also submit taped intervention sessions throughout the study, and the research team will review at least 20% of the recordings. In addition, a delivery assessment form will be completed after each contact with a caregiver, and the research team will review the forms to ensure adherence to the intervention protocol.

Furthermore, interventionists will use the intervention fidelity form to record the number and duration of home visits, telephone calls and sessions. Interventionists will also rate caregivers’ enactment in four aspects: data collection, home assignments, use of notebooks and use of written prescriptions [50]. A satisfaction questionnaire will be conducted after the intervention to collect information about participants’ satisfaction with specific components and with the quality of services [46].

#### Data collection procedures

After screening, interested and eligible caregivers will be scheduled for baseline assessment. They will be randomly assigned to one of the 16 experimental conditions (ECs) that vary the delivery of treatment components. Component 1 (Dementia and Caregiver Education) is compulsory and will be given to all participants as the core intervention (Table 1). Participants will be assessed at baseline (T0), 6 months of follow-up (T1) and 12 months of follow-up (T2) to objectively examine the immediate and long-term effects of the multicomponent intervention. All assessments will be conducted by well-trained part-time interviewers under close supervision. Once the caregivers have completed the entire intervention, they will receive monetary compensation (HKD 400) for their participation in the study.

#### Sample size estimation

In the fractional factorial MOST design, the sample size to detect main effects relies on the smallest clinically important difference between the presence and absence of a component, instead of the number of components evaluated. In view of this fact and previous research, an effect size of 0.60 (Cohen’s *d*) at 6 months is sufficient for a quasi-experimental pre − post treatment without control to determine the sample size [43]. A smaller effect size of 0.40 is selected to adopt a conservative approach. According to the power analysis, a sample size of 200 participants will give the study a power of 80% to detect the main effect or interaction effect size of 0.40 at an alpha of 0.5 with a two-tailed hypothesis test. Recruiting 250 participants will be sufficient assuming that the attrition rate is 20% over a 12-month period [43].

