Following the MOST framework, we will select the treatment components carefully to ensure that they are conceptually and operationally distinct from one another, so each component can be evaluated independently. However, we do not assume that the treatment components do not interact. Interaction effects may exist between individual components and influence primary outcomes. For example, during support group sessions, caregivers may exchange skills and information on managing the behavioural symptoms of care recipients by sharing and discussion; as such, the caregivers may build strong bonds and a sense of social support. As a result, behavioural symptom management component may moderate and strengthen the relationship between the support group component and perceived social support. In this regard, social support had a significant effect only when incorporated in multicomponent interventions instead of other domain-specific interventions [18]. Therefore, in the optimisation phase, we will use a factorial approach with effect coding to concurrently test the main effects of individual components and their interaction effects. All experimental conditions will involve education on dementia and caregiving as the core component, since it has been identified as the most ubiquitous component for caregiver support programmes as well as its ease of implementation. This factional factorial design will reduce the total number of conditions from 32 to 16, which retains the benefits of a factorial design whilst allowing a more logistically manageable and feasible study.

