#### Objectives

This study aims to:determine the implementation fidelity of each intervention component,assess the effect of each component on corresponding proximal outcomes,examine the effect of each component on primary outcomes (e.g. depression, burden),determine if the proximal outcomes of each component mediate the components’ effects on primary outcomes,determine the interaction effect between components on their proximal and primary outcomes anddetermine the moderating effect of the baseline scores of primary outcomes in the relationship between each intervention component and the corresponding outcome.

The hypotheses to be tested are as follows:The implementation fidelity of all six components is equally high.Components 2 (self-care skills), 3 (behavioural symptom management), 4 (behavioural activation), 5 (modified mindfulness-based cognitive therapy) and 6 (support group) will have significant effects on proximal outcomes, namely, self-care, dementia caregiving strategy, engagement in pleasurable activity, mindfulness and satisfaction with support group, respectively.Components 2–6 will have a stronger effect on their corresponding primary outcomes, namely, physical health status, stress/burden, psychological well-being, anxiety/depressive symptoms and social support, respectively, than the other components.Self-care, dementia caregiving strategy, engagement in pleasurable activity, mindfulness and satisfaction with support group mediate the relationship between component 2 and physical health status, between component 3 and stress/caregiving burden, between component 4 and psychological well-being, between component 5 and anxiety/depressive symptoms and between component 6 and social support, respectively.Component 3 moderates the relationship between component 6 and social support.The baseline scores of physical health status, stress/burden, psychological well-being, anxiety/depressive symptoms and social support moderate the effects of components 2–6 on changes in scores between the baseline and follow-up assessments of the corresponding outcomes.

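### The power statement prints alpha as 0.5, which does not reproduce its own 80%, and claims 80% power for an interaction of 0.40 without saying that this means a 0.80 SD difference between simple effects

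*Protocol article*

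**What the plan says.** The Sample size estimation section starts from an effect of 0.60 at 6 months and then reduces it: "A smaller effect size of 0.40 is selected to adopt a conservative approach". It states that 200 participants give 80% power "to detect the main effect or interaction effect size of 0.40 at an alpha of 0.5 with a two-tailed hypothesis test", and that recruiting 250 allows for 20% attrition. The section ties effect size to the difference between a component being present and absent, which defines it for a main effect. It gives no definition for an interaction. No other significance level appears in the article.

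On coding, the Introduction says "we will use a factorial approach with effect coding to concurrently test the main effects of individual components and their interaction effects". On interactions, Hypothesis 5 under Objectives reads "Component 3 moderates the relationship between component 6 and social support". The Data analysis section plans a test of component 3 by component 6 by time, with the T2 outcome as primary endpoint.

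**The concern.** Two things in one sentence need attention.

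1. A two-tailed alpha of 0.5 is ten times the conventional level and does not fit the sample size and power printed beside it. It is the only significance level the article gives, while the Data analysis section makes the significance of each factor its main objective. A reader checking the calculation cannot reproduce it as printed.

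2. Main effects and interactions share one detectable size, 0.40, but the same number does not describe the same thing for both. For a main effect it is the difference between having and not having a component. For an interaction it could be the effect-coded contrast, or the amount by which one component's effect changes when another is added. The second is twice the first. A reader who takes 0.40 as the change in component 6's effect when component 3 is added would believe the trial well powered for a modest moderation. On that scale, 80% power applies only to a change of about 0.80 SD.

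**Working it through.** **Inputs.** From Sample size estimation: 200 analysable participants, effect 0.40, two-tailed test, 80% power, 20% attrition. From Table 1: each component is present in 8 of 16 conditions, and each pair of components splits the conditions 4/4/4/4. With equal condition sizes (assumed), this gives 100 v 100 for a main effect and 50 per cell for a pair. The outcome SD is set to 1.

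**Table 1.** Every condition has an even number of absent components among components 2 to 6. It is therefore a balanced half fraction, and the five main effects and ten two-way interactions are mutually orthogonal (checked numerically). The simple standard errors below apply.

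**The plan's own figure.** The SE of a main effect is √(1/100 + 1/100) = 0.141, and 0.40/0.141 = 2.828.

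| Alpha | Critical z | Power, normal | Power, noncentral t | Total N for 80% |
|---|---|---|---|---|
| 0.5 two-sided (as printed) | 0.674 | Φ(2.828 − 0.674) = 98.4% | 98.5% | 58 (54 by exact two-tailed t) |
| 0.05 two-sided | 1.960 | Φ(2.828 − 1.960) = 80.7% | 80.4% | 198 |
| 0.5 one-sided | 0 | 99.8% | – | 18 |
| 0.05 one-sided | 1.645 | 88.2% | – | 156 |

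Of these, only two-sided 0.05 reproduces 200 and 80%. Attrition: 200/(1 − 0.20) = 250, as stated.

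**Interaction.** Let D be the difference of differences: component 6's effect with component 3 present, minus its effect with component 3 absent.

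- SE of D = √(4/50) = 4/√200 = 0.283.
- The effect-coded interaction, on the same scale as a main effect, is D/2. Its SE is 0.141, the same as for a main effect.
- Effect-coded 0.40 means D = 0.80. Then 0.80/0.283 = 2.828, and power is 80.7% (t: 80.3%), matching the plan.
- D = 0.40 gives 0.40/0.283 = 1.414, and power is Φ(1.414 − 1.960) = 29.3% (t: 29.0%).
- Smallest D with 80% power: (1.960 + 0.842) × 0.283 = 0.79 SD. The matching main effect is (1.960 + 0.842) × 0.141 = 0.396 SD.
- If all 250 were retained, power for D = 0.40 would be 35%.
- 80% power for D = 0.40 needs 16 × (2.802/0.40)² ≈ 785 analysable participants.

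**Sensitivity to baseline adjustment.** The protocol gives no baseline correlation r, so the values below are assumptions. Adjusting for baseline multiplies the SE by √(1 − r²).

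| Assumed r | Power for D = 0.40 | Detectable D at 80% power |
|---|---|---|
| 0 | 29% | 0.79 |
| 0.5 | 37% | 0.69 |
| 0.7 | 51% | 0.57 |
| 0.8 | 65% | 0.48 |

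Power for D = 0.40 reaches about 80% only near r = 0.86 (79%).

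**The case against.** The strongest reply on alpha is that it is a slip of one digit with no effect on the design. That stands. The figure occurs only in the sample size paragraph, the Data analysis section sets no threshold of 0.5, and 200 and 250 follow from 0.05. A reader might infer that the trial will be judged at 0.5; nothing in the article supports that. The printed value is nonetheless wrong and is the only one given.

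On the interaction, the reply is that equal power for main effects and two-way interactions is a known property of an effect-coded balanced factorial, and that the article names effect coding. That also stands: the 80% is not an arithmetic error. What remains is that the section defines 0.40 only as component present against absent and never says what an interaction of that size means.

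Three stronger readings are tempting and unsupported:

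- *The true interaction power is 29%.* That is the power for a 0.40 SD difference of differences without baseline adjustment. The protocol does not claim to be powered for that difference, and it plans mixed models over three time points. Hypothesis 5 states moderation without a size or scale.
- *A null interaction will be read as no interaction.* No passage says so.
- *The choice of combination rests on interactions.* The Abstract uses component effects and interactions together, and the Discussion lists interactions among the secondary objectives.

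**Conclusion.** The concern holds in two parts of different weight.

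Alpha of 0.5 is a definite error. It gives about 98.5% power at 200 where the plan states 80%, and two-sided 0.05 restores agreement. It must be corrected, though it changes nothing in the design.

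The interaction claim is formally correct under effect coding but incompletely stated. Its 80% power applies to a 0.80 SD difference between simple effects, twice the 0.40 SD main effect. This calls for a clarification and is not a fault in the calculation. It rests on equal condition sizes, 200 analysable participants, and no variance reduction from baseline. With baseline adjustment the detectable difference would fall to 0.69 SD at an assumed correlation of 0.5 and to 0.48 SD at 0.8. Power for a 0.40 SD difference stays below 80% across that range.

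**What to change.** Correct alpha to 0.05. Then restate the power sentence along these lines: *200 analysable participants give 80% power at two-sided alpha 0.05 for a main effect of 0.40 SD, or for a two-way interaction equal to a 0.80 SD difference between simple effects (effect-coded 0.40).* Alternatively, limit the 80% claim to main effects.

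If power for a 0.40 SD difference is quoted, give it as about 29% with no baseline adjustment and about 37% to 65% for assumed baseline correlations of 0.5 to 0.8, and label the correlations as assumptions.

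The cost is about two sentences. The targets of 200 and 250 stand, and no change to design or recruitment follows (recruitment closed on 31 December 2022 according to Trial status). The interaction claim will read less favourably than it does now.

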#### Data analysis

This study will adopt the principle of intention-to-treat for data analysis of the individual intervention components (components 2–6). The main objective is to examine the level of significance of each factor on proximal and primary outcomes by using linear mixed models at three time points (T0, T1 and T2). Linear mixed regression models account for repeated measures within participants and handle missing data using maximum likelihood estimation in a longitudinal dataset without needing multiple imputations [51]. The pre − post within group difference will also be investigated (i.e. T1 vs. T0 and T2 vs. T0). On the one hand, the across time difference of each component can be viewed as the main effect. On the other hand, such effect will be modelled as components by time interactions, with T2 outcome as the primary endpoint. The study will also include the analysis for two-way interactions between components (i.e. factor 3 by factor 6 by time interaction).

The examination of moderation and mediation effects of significance will follow the guidelines established by MacKinnon and Luecken [52]. To detect the underlying mechanism of components, the study will test for fit of the mediation model. The relationship path between each component and their respective primary outcomes will be established. The pathway between the components and proximal outcomes and between the proximal and primary outcomes will be investigated. The relationship between the components and primary outcomes mediated by the proximal outcomes will be investigated. When testing the fit of the moderation model, the relationship between each component and the change of primary outcome will be examined. Afterwards, the strength and direction of the relationship will be tested again accounting for the effects of the baseline primary outcomes. The moderation models will be used to identify the interaction effects of the matching risk profiles of caregivers with specific components. The moderating effects of the matching profiles with components have never been explored in previous studies.

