**Methods:**

A prospective, assessor-blinded, randomised clinical trial with fractional factorial design using the MOST principle. Two hundred fifty family dementia caregivers will be randomised to one of 16 experimental conditions in a fractional factorial design involving six intervention components: (1) dementia and caregiving education; (2) self-care skills; (3) behavioural symptom management; (4) behavioural activation; (5) modified mindfulness-based cognitive therapy; and (6) support group. The first one is the core component, and the five remaining will be examined. Physical health, caregiver burden, stress, psychological well-being, anxiety and depressive symptoms, and social support will be assessed over the 12-month study period. Following the intention-to-treat principle, linear mixed models and regression analyses will be used to examine the specific effect of the five components and their two-way interactions to propose the most effective combination.

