Another major limitation of studies on multicomponent interventions is that researchers often omit to report whether components have been implemented with fidelity; thus, the implementation fidelity of individual components remains unknown [19]. Assessment of implementation fidelity is an important first step in determining the effectiveness of a treatment component. Moreover, to our knowledge, no previous study has examined the underlying mechanism of individual components of multicomponent interventions. The factorial design of single intervention components will enable us to determine not only which components are the most strongly associated with changes in primary outcomes but also the fidelity of the implementation of each component, the components that lead to improvements in corresponding proximal outcomes (i.e. the goal of the component) and whether the proximal outcomes mediate the effects of their corresponding components on primary outcomes (i.e. understand the underlying mechanism of each component).

Multicomponent interventions can be tailored to meet the specific needs of individual caregivers given the variability inherent in caregiving situations [8]. Specific treatment modules or strategies and techniques may be applied according to the risk profiles of caregivers to provide personalised support. However, whether such matching between the risk profiles of caregivers and individual components works better than a one-size-fits-all approach remains unknown because the relative efficacy of a specific component on a specific outcome has yet to be examined systematically. Hence, this study will also determine the moderating effects of the baseline scores of primary outcome measures in the relationship between intervention components and primary outcomes.

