### Discussion

As the dementia tsunami approaches, effective family caregiver interventions are essential to improve the health outcomes of the caregiver–care recipient dyads and delay nursing home placement. Multicomponent interventions are promising strategies to support dementia caregiving but will provide a bundled treatment package, which may be associated with increased cost if inactive components are provided or if more than what is necessary is delivered. By using the MOST framework, we can identify the individually effective components of multicomponent interventions for dementia caregiving. This proposed study extends and clarifies our prior work [8–10, 13, 15, 54], indicating the efficacy of a multicomponent package of interventions to support the physical and psychosocial well-being of dementia caregivers.

We have described the protocol for a MOST fractional factorial trial aimed to optimise the multicomponent interventions for dementia caregivers. The primary objective of this study is to estimate the specific effect of each of the five components on its corresponding primary outcomes within 6 months and propose the most effective and efficient combination of components for dementia caregivers. The study has several secondary objectives, including the exploration of implementation fidelity, the main effects and the interactions of each component and the matching between treatments and individual characteristics to support dementia caregivers over the course of 12 months. The proposed trial is significant in representing the first principled and systematic effort to design an effective, efficient and potentially personalised intervention to meet the modest demands of dementia caregivers, such that all of its components (education, training on self-care skills, behavioural symptom management, behavioural activation, mindfulness and support group) are active and feasible for real-world implementation.

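### The Data analysis and Discussion sections state different primary questions (every component on the primary outcomes at 12 months, or each component on its own outcome within 6 months), and the two can retain different components

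*Protocol article*

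**What the plan says.** Primary outcome measures lists seven instruments: SF-12 physical component, ZBI, PSS, Ryff's scale, HADS-A, PHQ-9 and MOS-SSS. Five components (2 to 6) are tested. The article describes the primary question in two ways.

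- **Wide.** Data analysis: "The main objective is to examine the level of significance of each factor on proximal and primary outcomes". Nothing in that sentence limits a factor to its own outcome, and the same paragraph makes T2 (12 months) the primary endpoint. Objective 3 is similarly open: "examine the effect of each component on primary outcomes (e.g. depression, burden". The Introduction speaks of finding "which components are the most strongly associated with changes in primary outcomes".
- **Matched.** In the Discussion the primary objective is to "estimate the specific effect of each of the five components on its corresponding primary outcomes", on a six-month horizon. The same sentence ties this to proposing the combination. The next sentence places the components' main effects and interactions, followed over 12 months, among the secondary objectives. Hypotheses 3 and 4 in Objectives use the same pairing.

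The Abstract's end product comes from the component effects and "their two-way interactions to propose the most effective combination". On error control, Sample size estimation has one calculation for one effect, "at an alpha of 0.5 with a two-tailed hypothesis test".

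**The concern.** The trial's product is a decision about which components go into the recommended package. What Data analysis calls the main objective overlaps with what the Discussion calls secondary, and the two sections also use different time points. The result can turn on the reading. Suppose the mindfulness component misses on HADS-A and PHQ-9 but reaches p<0.05 on PSS. Under the Discussion's objective it has failed on its own outcomes. Under the Data analysis sentence it has shown an effect on a primary outcome and could be retained.

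The wider the set of contrasts that can support a component, the more often an inert one gets through. The Discussion itself names the cost of delivering inactive components as the problem with bundled packages.

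**Working it through.** **1. The plan's own figure.** Inputs from Sample size estimation: d = 0.40, 80% power, 200 evaluable, 20% attrition, "with a two-tailed hypothesis test". Table 1 puts 8 of the 16 conditions at each level of every component, so 100 v 100.

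n per level = 2(1.960 + 0.842)² / 0.40² = 2 × 7.85 / 0.16 = 98.1, rounded up to 99, or 198 in total. This agrees with "a sample size of 200 participants will give the study a power of 80" per cent (power at 100 v 100 is 80.4% by noncentral t). Recruitment: 200 / 0.80 = 250, as stated. The printed alpha of 0.5 would give 98.4% power, or need only 58 participants for 80%. Two-sided 0.05 is therefore taken as the intended level. The calculation covers one test.

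**2. Counting contrasts.**

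| Component | Matched instruments | Number |
|---|---|---|
| 2 self-care | SF-12 physical | 1 |
| 3 behavioural symptoms | ZBI, PSS | 2 |
| 4 behavioural activation | Ryff | 1 |
| 5 mindfulness | HADS-A, PHQ-9 | 2 |
| 6 support group | MOS-SSS | 1 |

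Matched: 1 + 2 + 1 + 2 + 1 = 7. Wide: 5 × 7 = 35, of which 35 − 7 = 28 are unmatched. Ryff is counted once, as a total. The 35 leaves out proximal outcomes, the other time point and interactions, so it is not an upper bound for the wide reading.

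**3. Error rates.** Assumptions: all five components inert, each contrast at unadjusted two-sided 0.05, and a common correlation ρ between instruments. Tests of different components are treated as independent, because the five columns of Table 1 are mutually orthogonal. Let p7 be the chance that one inert component reaches significance on at least one of the seven instruments, and p2 the same for two matched instruments.

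- Matched family: 1 − 0.95³ × (1 − p2)²
- Wide family: 1 − (1 − p7)⁵

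| ρ | p2 | p7 | 7 matched | all 35 |
|---|---|---|---|---|
| 0 | 9.8% | 30.2% | 30.2% | 83.4% |
| 0.3 | 9.5% | 27.1% | 29.8% | 79.5% |
| 0.5 | 9.1% | 23.0% | 29.1% | 72.9% |
| 0.8 | 7.8% | 14.9% | 27.1% | 55.3% |

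At ρ = 0: p2 = 1 − 0.95² = 9.8%, p7 = 1 − 0.95⁷ = 30.2% and 1 − 0.95³⁵ = 83.4%. At ρ = 0.5: 1 − 0.857 × 0.909² = 29.1% and 1 − 0.770⁵ = 72.9%.

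**4. Per component.** If one significant primary instrument of any kind were enough to retain a component, an inert one would be kept 15% to 27% of the time (ρ from 0.8 to 0.3). If only matched outcomes count, the figure is 5% for components 2, 4 and 6, and about 8% to 9.5% for components 3 and 5 over the same range.

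**The case against.** The matched reading has strong support. Hypotheses 2, 3, 4 and 6 pair components with outcomes, the mediation text in Data analysis refers to each component's respective outcome, and the Discussion ranks objectives as primary and secondary. The Data analysis sentence could be a loose summary of the modelling, since it does not say every factor on every outcome. A multiplicity rule may also sit in an analysis plan that is not shown.

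Much of this stands, and it rules out several stronger readings.

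- A reader might infer that the article never names a primary family. It does, in the Discussion. The fault is that Data analysis names another.
- A reader might infer that every contrast is tested at full alpha, so that the false-positive rate is some 5 to 15 times nominal. The article states no testing rule. Each single test keeps its 5%, and the multiples describe a family-wise rate with everything inert and no adjustment.
- A reader might infer that the final package would probably contain a useless component. That needs the any-instrument retention rule, which the article does not state, and several inert components. At 23% each, the chance is 23% with one inert component, 1 − 0.77² = 41% with two and 1 − 0.77³ = 54% with three.
- A reader might treat the unmatched contrasts as dispensable. Hypothesis 3 says each component affects its own outcome more than the other components do, so they are needed as comparators.

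None of this reconciles the two sections. An unseen analysis plan does not remove a contradiction between two statements in the article, and the time points differ however loosely the Data analysis sentence is read.

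**Conclusion.** The point holds as a contradiction between Data analysis and the Discussion over which component-by-outcome contrasts, and which time point, are primary. Objective 3 shares the wide wording. The two readings can lead to different packages.

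The size is conditional. With all components inert and unadjusted two-sided 0.05 tests, the family-wise error rate is about 27–30% for the matched family and about 55–83% for the wide one. An inert component's chance of being retained is about 15–27% if any primary instrument suffices, against 5% to about 9% on its matched outcomes. These figures rest on an assumed between-instrument correlation, on 0.05 as the intended alpha, and on a retention rule the article does not state. They show what depends on the choice of reading and are not the trial's actual error rate. Whether to adjust within the seven matched contrasts is a matter for the analysis plan and is not part of this point.

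**What to change.** Before outcomes are analysed by allocation:

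1. Reword the main-objective sentence in Data analysis, and objective 3, to agree with the Discussion. The primary family is the seven matched contrasts: component 2 on SF-12 physical; 3 on ZBI and PSS; 4 on Ryff; 5 on HADS-A and PHQ-9; 6 on MOS-SSS. These decide whether a component is called active.
2. Reconcile T2 with the Discussion's six-month horizon and name one primary time point in both places.
3. Keep the 28 unmatched contrasts as comparators for Hypothesis 3. Otherwise label them exploratory, together with the other time point and any interaction not hypothesised. The component 3 by component 6 interaction on social support is hypothesised and keeps its place.

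This costs wording only: no participants, no visits and no power on the matched contrasts. The downside is small: a significant result on an unmatched outcome can no longer support a claim by itself.

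### With T0 modelled as a response and no equal-baseline constraint stated, each component test is a difference in change from T0: valid, but less precise than baseline adjustment for every outcome measured at T0

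*Protocol article*

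**What the plan says.** In the Data analysis section, proximal and primary outcomes are analysed "by using linear mixed models at three time points (T0, T1 and T2", and for the component effects "such effect will be modelled as components by time interactions, with T2 outcome as the primary endpoint". T0 is thus one of the modelled responses. Baseline scores are adjusted for only in the later moderation analysis, where "the strength and direction of the relationship will be tested again accounting for the effects of the baseline primary outcomes". For the main models the section mentions no baseline covariate and no constraint on T0 means.

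The Sample size estimation section bases the size on "the smallest clinically important difference between the presence and absence of a component". It says "A smaller effect size of 0.40 is selected to adopt a conservative approach" and concludes that "a sample size of 200 participants will give the study a power of 80" per cent "at an alpha of 0.5 with a two-tailed hypothesis test" (that is how alpha is printed). It then adds: "Recruiting 250 participants will be sufficient assuming that the attrition rate is 20% over a 12-month period". It gives no within-person correlation and does not say which SD scales d.

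The sections on allocation and on data collection both place random assignment after the baseline assessment.

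**The concern.** When T0 is a response and each component may have its own effect at T0, the component-by-time term at T2 is the difference between levels in mean change from T0. That model spends information estimating T0 differences which randomisation has already made zero in expectation. Constraining them to zero, or conditioning on T0, recovers that information.

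What is at stake is precision in the component main effects, and in the two-way interactions that the protocol sizes at the same d. In an optimisation trial, a missed effect can lead to an active component being dropped. According to the Trial status section, recruitment ended on 31 December 2022. The sample size is therefore fixed, and the analysis model is what can still be improved.

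**Working it through.** **Inputs.** From Sample size estimation: d = 0.40, 200 evaluable, 80% power, two-sided, 250 recruited, 20% attrition. From Trial design: each main effect compares eight conditions with eight, taken as 100 v 100. Assumed, because the protocol does not give them: rho; d in outcome-SD units; equal SDs at T0 and T2.

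**The plan's own figure.** SE = 2/√200 = 0.1414. Power = Φ(0.40/0.1414 − 1.960) = Φ(0.868) = 0.807, and 200/0.80 = 250. The stated figures therefore reproduce as a two-group comparison with unit SD, no correlation term and alpha 0.05. At the printed alpha of 0.5, power would be 0.984 and the required total 58. That misprint is a separate matter, and 0.05 is used throughout here.

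**The two analyses.** SE = 0.1414 × √v, with v = 2(1 − rho) for difference in change and v = 1 − rho² for baseline adjustment. The ratio of adjusted to change variance is (1 − rho²)/[2(1 − rho)] = (1 + rho)/2, never above 1. The ordering does not need equal SDs: if the T0 SD is k times the T2 SD, then v for change is 1 + k² − 2k·rho, which exceeds 1 − rho² by (k − rho)² ≥ 0.

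Example at rho 0.3. Change: SE = 0.1414 × √1.40 = 0.1673, power = Φ(2.390 − 1.960) = 0.667. Adjusted: SE = 0.1414 × √0.91 = 0.1349, power = Φ(2.965 − 1.960) = 0.843.

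| rho | v, change | power | v, adjusted | power |
|---|---|---|---|---|
| 0.3 | 1.40 | 0.667 | 0.91 | 0.843 |
| 0.4 | 1.20 | 0.733 | 0.84 | 0.870 |
| 0.5 | 1.00 | 0.807 | 0.75 | 0.904 |
| 0.6 | 0.80 | 0.885 | 0.64 | 0.942 |
| 0.7 | 0.60 | 0.955 | 0.51 | 0.977 |

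**Threshold for 80%.** This needs v ≤ 50 × (0.40/2.8016)² = 1.019, so rho ≥ 1 − 1.019/2 = 0.490. At rho 0.3 the change test would need 276 evaluable (345 recruited). At rho 0.5 it needs 198 (248 recruited), against 148 (185 recruited) with adjustment.

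**Partial data from dropouts.** Maximum likelihood also uses the visits of those who leave. With 125 per level at T0, 100 at T2 and compound symmetry, generalised least squares gives the unconstrained model power of 0.792–0.798 at rho 0.45 and 0.806–0.812 at rho 0.47. The range reflects how many dropouts contribute T1. The threshold falls to about 0.46. At rho 0.5 the comparison is 0.827–0.833 unconstrained against 0.904–0.910 constrained.

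**If d is in change-SD units.** The change test has power 0.807 at any rho. Adjustment still gains: power = Φ(2.828/√[(1 + rho)/2] − 1.960). At rho 0.5 this is Φ(2.828/0.866 − 1.960) = Φ(1.306) = 0.904.

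**The case against.** The strongest reply is that the protocol never says T0 means are left free. A constrained longitudinal model is also a mixed model on three visits with component-by-time terms, and such detail often sits in an analysis plan that is not shown here. This stands in part: the free-baseline model is the ordinary reading, not an explicit statement. But the article does state the responses and the tested term, and it mentions baseline adjustment only for moderation. If the constraint is already intended, one sentence closes the point.

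The second reply concerns the scale of d. The protocol takes 0.40 as a reduction from a pre–post effect of 0.60, so a change-SD scale is plausible, although the presence-versus-absence wording points to the outcome SD. This stands fully, and any power threshold is conditional on it.

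A reader might infer more than the document supports:

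- *That the trial is underpowered.* Neither rho nor the SD scale is given, and at rho 0.5 or above the planned test meets its target.
- *That the baseline is wasted.* It is used by subtraction, which beats a T2-only comparison when rho exceeds 0.5.
- *That the sample size matches neither analysis.* At rho 0.5 the change contrast has v = 1.00, exactly the calculation that reproduces the stated power.
- *That every component test is affected.* Satisfaction with the support group is measured only after the intervention, so it has no T0 value.
- *That chance baseline imbalance biases the test.* Under randomisation it does not. Its effect is already counted in the larger variance.

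**Conclusion.** The point holds as one of efficiency, not validity. On the ordinary reading, the planned contrast has 2/(1 + rho) times the variance of the baseline-adjusted one: 1.54 at rho 0.3, 1.33 at rho 0.5 and 1.18 at rho 0.7. This applies to outcomes measured at T0, and the multiples assume equal SDs at T0 and T2.

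Whether the stated 80% is reached depends on quantities the protocol does not give. With d in outcome-SD units and equal SDs, the planned test needs rho of about 0.46 (dropouts' data used) to 0.49 (completers only), while the adjusted analysis does not fall below 0.807 at any rho. With d in change-SD units the stated power holds and only the efficiency loss remains. This is a free improvement rather than the correction of an error.

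**What to change.** In Data analysis, state that the mixed model has a common T0 mean for all conditions: time effects, plus effect-coded components and their two-way interactions at T1 and T2 only, with an unstructured covariance. Alternatively, model T1 and T2 with T0 as a covariate; the two are close but not identical when data are missing. Read each effect at the primary time point, which this section gives as T2. Analyse outcomes without a T0 value separately.

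In Sample size estimation, state whether d = 0.40 is in units of the outcome SD or of the change SD, and give the correlation assumed if one was used.

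The cost is a few sentences of model wording, with no new data and no loss of validity under randomisation. The change should be fixed and dated before outcome data are compared by condition.
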